#### General Instructions

Participants will be provided with a brief overview of the study procedures and a description of the 5 specimen self-collection kits contained in the box. They will be informed that they can choose to self-collect and return all, some, or none of the specimens depending on their comfort levels. They will also be informed that the box includes 2 prepaid shipping envelopes affixed with FedEx labels—#1 for biological specimens to be returned to the Emory University Clinical Virology Research Laboratory in Atlanta for HIV, gonorrhea, and chlamydia testing (ie, a finger-stick blood sample, pharyngeal swab, rectal swab, and urine specimen) and #2 for a hair sample to be returned to the Hair Analytical Laboratory (HAL) at the University of California, San Francisco (UCSF).

#### Specific Instructions

Each specimen self-collection kit will contain simple step-by-step written instructions accompanied by color images provided by the laboratories.

Finger-stick blood sample self-collection kit (for HIV testing): Participants will be instructed to wash their hands with soap and warm water, clean their middle or ring finger from their nondominant hand using the alcohol wipe, stimulate blood flow by shaking their hand below the waist for 15 seconds, prick their chosen finger using the safety lancet, wipe away the first drop of blood using the sterile gauze, collect blood using the capillary into the transport tube marked with a fill line, secure the transport tube’s cap, apply the bandage to their finger, gently mix the blood with the anticoagulant in the transport tube by flipping it upside down, and finally place the tube in the provided biohazard bag.Pharyngeal swab self-collection kit (for gonorrhea and chlamydia testing): Participants will be instructed to open their mouth wide, wipe the swab around their tonsils on both sides of their throat, place it in the transport tube, screw the transport tube’s cap back on securely, and finally place the tube in the provided biohazard bag.Rectal swab self-collection kit (for gonorrhea and chlamydia testing): Participants will be instructed to apply 1 drop of lubricant to the tip of the swab, insert it approximately 1.5 inches into their rectum, gently rotate it for 5 to 10 seconds in a circular motion, withdraw it carefully and place it in the transport tube, screw the transport tube’s cap back on securely, and finally place the tube in the provided biohazard bag.Urine specimen self-collection kit (for gonorrhea and chlamydia testing): Participants will be instructed to collect the first part of their urine stream into a sample collection cup marked with a fill line, use a pipette to transfer urine from the cup into the transport tube, repeating the process until the tube is filled between the minimum and maximum fill lines, screw the transport tube’s cap back on securely, and finally place the tube in the provided biohazard bag.Once all specimens (intended to be returned by a participant) have been placed in the biohazard bag, participants will be informed that they should seal it and place it in the prepaid shipping envelope #1 to be returned to the Emory University Clinical Virology Research Laboratory.Hair sample self-collection kit (to assess adequacy for potential PrEP adherence monitoring in the future): Participants will be instructed to clean scissor blades with the alcohol wipe, cut a segment of hair (about 20 to 30 fibers) from the side of their head as close to their scalp as possible, tape the hair sample to the piece of aluminum foil with an adhesive label placed on the hair end furthest from the scalp, fold the foil shut, and finally place it in the clear plastic bag provided.Once the hair sample (intended to be returned by a participant) has been placed in the clear plastic bag, participants will be informed they should seal it and place it in the prepaid shipping envelope #2 to be returned to the HAL at UCSF.

Specimen return is completely voluntary, and no incentives will be provided to participants for completing this step. Returned finger-stick blood samples, pharyngeal swabs, rectal swabs, and urine specimens will be tested for HIV, gonorrhea, and chlamydia at the Emory University Clinical Virology Research Laboratory and returned hair samples will be visually inspected for adequacy for PrEP drug level testing at the HAL at UCSF. HAL staff have analyzed tens of thousands of hair samples for TFV and FTC concentrations and can readily determine by visual inspection if the self-collected specimens are adequate for potential PrEP adherence monitoring. No identifiable information will be provided to laboratory personnel at Emory University or UCSF, and the specimens will be connected to the results solely on the basis of the box ID. Results will be returned to the study staff at UMSN through a password-protected file shared over Box, a secure cloud storage and collaboration platform approved by the University of Michigan.

HIV, gonorrhea, and chlamydia test results will be delivered back to participants by trained counselors over the phone. Each of the counselors will have experience in the provision of HIV Counseling, Testing, and Referral. They will therefore have experience in answering participants’ questions about the HIV and STI testing processes, addressing concerns around sexual risk behaviors, and initiating linkage to care. For anyone testing positive for HIV, gonorrhea, or chlamydia, the study staff will compile a list of local treatment providers in their area using resources such as United Way 2-1-1 [105] and Emory University’s AIDSVu testing and treatment locator [106]. Participants with positive test results will be counseled about the importance of accessing treatment, notifying their sexual partners, and sexual risk reduction measures. Within 24 hours of delivering the positive test results, the study staff will send them an email including a list of local treatment providers. Participants will be contacted by phone 2 more times: (1) 2 weeks after the initial delivery of positive test results to confirm whether or not an appointment was made and (2) 4 weeks after the initial delivery of positive test results to assess engagement in care and provide any additional resources requested. Participants testing negative for HIV, gonorrhea, and chlamydia will be counseled about the importance of regular screening and engaging in safe sexual behaviors. For anyone testing negative for HIV and not on PrEP, the study staff will provide more information about this prevention option. During the phone call to return HIV and STI test results, participants will also be informed about whether the self-collected hair samples they returned were of adequate quality for potential PrEP adherence monitoring. If a participant’s hair sample quality analysis results have not been received before their HIV, gonorrhea, and chlamydia results, the study staff will follow-up with participants as soon as they are available (ie, the return of HIV and STI test results will be prioritized).

Participants will be given 6 weeks from box delivery to collect their biological specimens and return them by mail for laboratory processing. Those who have returned some or all of their specimens will be emailed a link to a short posttest survey, within 24 hours of the results delivery phone call. The survey, programmed in Qualtrics, will assess any change in their previous willingness and perceived ability to self-collect and return different types of specimens since using the specimen self-collection kits. Participants who have not returned any specimens within 6 weeks of box delivery will also be emailed a link to the posttest survey at that time point to assess any change in their previous willingness and perceived ability to self-collect and return specimens after seeing or attempting to use the 5 different types of specimen self-collection kits. The survey will also include questions to elicit reasons for not returning each type of specimen using lists of pre-specified options, as well as open-ended response fields. The posttest survey will take approximately 10 min to complete, and participants will receive an incentive of US $10 in the form of an Amazon gift card.

Similar to the baseline survey, after participants have been sent the original email containing a link to the posttest survey, they will receive up to 3 reminders at weekly intervals using their preferred communication method indicated during registration (email, phone call, or text). The final reminder will advise participants that noncompletion of the survey within the next 7 days will suggest that they are no longer interested in continuing, unless they contact study staff and ask for an extension. Participants who do not complete the posttest survey within 7 days of receiving the final reminder (ie, by the end of 4 weeks after the original email has been sent) will no longer be contacted.

### Phase 1 Outcomes

Specific outcomes to be measured during this phase include— *Information:* (1) Pre-existing awareness of commercially available self-collection kits for home-based HIV testing, (2) Knowledge of transmission and prevention of HIV and other STIs, and (3) Variations in knowledge levels across categories of selected characteristics (eg, age, race and ethnicity, educational level, sexual orientation, HIV and bacterial STI testing history, relationship status, sexual behaviors, experiences with medical care, substance use, and psychological distress); *Motivation:* (1) Theoretical willingness to self-collect and return each of the 5 different types of biological specimens, (2) Actual return of each type of specimen, defined as the receipt of prepaid shipping envelopes back at the laboratories within 6 weeks of box delivery to participants, and (3) Reasons for not returning certain types of specimens; and *Behavioral skills:* (1) Perceived ability to self-collect and return each of the 5 different types of biological specimens and (2) Adequacy of specimens to conduct actual laboratory testing for HIV, gonorrhea, and chlamydia (determined by testing returned finger-stick blood samples, pharyngeal swabs, rectal swabs, and urine specimens) and potential laboratory testing for PrEP drug levels (determined by visually inspecting returned hair samples).

### Phase 1 Analytic Plan

Descriptive statistics (means, medians, and interquartile ranges for continuous variables, and counts and proportions for categorical variables) will be used to characterize the demographic and behavioral characteristics of the sample (including HIV and bacterial STI testing history) using software for quantitative data analysis (SAS). Analyses paralleling the IMB model include— *Information:* (1) Proportions of participants who are aware of commercially available self-collection kits for home-based HIV testing will be estimated, (2) Scores for the knowledge of transmission and prevention of HIV and other STIs will be formulated for each participant, and (3) Variations in knowledge levels across categories of selected characteristics will be assessed using chi-square tests for homogeneity; *Motivation:* (1) Frequency distributions of participants’ theoretical willingness to self-collect and return each of the 5 different types of biological specimens will be plotted, (2) Proportions of each type of specimen actually returned will be calculated and compared with theoretical willingness using Fisher exact tests across categories of selected characteristics (eg, age, race and ethnicity, educational level, sexual orientation, HIV and bacterial STI testing history, relationship status, sexual behaviors, experiences with medical care, substance use, and psychological distress), and (3) Reasons for not returning certain types of specimens will be tabulated, including manually reviewing and reassigning open-ended responses to appropriate pre-specified options; and *Behavioral skills:* (1) Frequency distributions of participants’ perceived ability to self-collect and return each of the 5 different types of biological specimens will be plotted and (2) Proportions of each type of returned specimen that are deemed adequate for actual laboratory testing (for HIV, gonorrhea, and chlamydia) and potential laboratory testing (for PrEP drug levels) will be calculated. Frequencies and proportions of positive and negative HIV, gonorrhea, and chlamydia test results and linkage to care statistics will also be aggregated.

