## Methods

### Study Overview

Project Caboodle! is an exploratory 2-year study to obtain both quantitative and qualitative data regarding the acceptability and feasibility of biological specimen self-collection and return from sexually active HIV-negative or unknown status MSM aged 18 to 34 years residing in the United States or dependent areas. In Phase 1, we will send 100 participants a box containing instructions and materials for self-collecting and potentially returning a finger-stick blood sample (for HIV testing), pharyngeal swab, rectal swab, and urine specimen (for gonorrhea and chlamydia testing), and hair sample (to assess adequacy for potential PrEP adherence monitoring in the future). Specimen return is not incentivized, and participants can choose to mail back all, some, or none of these 5 specimens. In Phase 2, we will conduct individual in-depth interviews using a video-based teleconferencing software (VSee) with 32 participants from Phase 1 to examine attitudes toward and barriers to self-collecting and returning each type of specimen.

Guided by the theoretical constructs of the Information-Motivation-Behavioral skills (IMB) model [88,89], the specific aims of our study are as follows:

*Aim 1:* Explore the acceptability and feasibility of self-collecting at home and returning by mail all, some, or none of the following biological specimens: (1) finger-stick blood sample, (2) pharyngeal swab, (3) rectal swab, (4) urine specimen, and (5) hair sample, among 100 sexually active HIV-negative or unknown status US MSM (aged 18 to 34 years, 50 black and 50 white including those of Hispanic ethnicity) recruited through social media platforms.*Aim 2:* Collect qualitative data via individual in-depth interviews conducted using VSee from 2 subsamples of 16 MSM each, including participants who (1) returned all 5 specimens and (2) returned some or no specimens to examine attitudes toward and barriers to completing various study activities.

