### Participant Recruitment

Project Caboodle! will recruit and enroll 100 young (aged 18 to 34 years), sexually active HIV-negative or unknown status MSM residing in the United States. Participants will be recruited online using age-appropriate, racially and ethnically diverse advertising on social networking websites (eg, Facebook and Instagram) and mobile gay dating apps (eg, Grindr and Scruff). We will aim to ensure that our sample includes equal numbers of black and white MSM including those of Hispanic ethnicity. Our advertisements will include images of men hugging, kissing, or holding hands, the study logo, and call-to-action text. These will appear as posts on social networking websites and will be targeted to profiles reflecting gay *interests*, that is, topics users have accessed (eg, same-sex marriage), and pages they have *liked* (eg, pride events).

Individuals who click on our advertisements will be directed to our study’s landing page (programmed in Qualtrics, a secure Web-based platform approved by the University of Michigan) that will provide a brief overview of the study protocol, in addition to basic information on the burden of HIV and bacterial STIs among MSM in the United States. Those who are not interested can exit by closing the landing page in their browser. Interested individuals can click a button to continue, which will direct them to a comprehensive informed consent document. This document will provide information regarding our study’s purpose, contents of the eligibility screener, the baseline survey, and the posttest survey, study procedures in Phases 1 and 2, potential risks of participation, and the right to refuse participation or withdraw at any time. Individuals will be asked to provide consent to (1) be screened for eligibility, (2) be asked for their contact information, (3) participate in the biological specimen self-collection activities (ie, Phase 1) if they meet the eligibility criteria, and (4) be potentially asked to participate in an in-depth interview (ie, Phase 2).

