### Phase 1 Procedures

Registered participants will be sent an email containing a link to the baseline survey, programmed in Qualtrics. The survey will include questions pertaining to the following domains— *demographic characteristics:* data on age, race and ethnicity, educational level, sexual orientation, employment status, history of incarceration, history of homelessness, health insurance coverage, and access to health care will be collected [94]; *HIV testing history:* participants will be asked about whether they have ever been tested for HIV, the time frame of their most recent test, the location of their most recent test, and their annual frequency of testing or their reasons for never testing [81,86,94]; *home-based HIV testing:* data will be collected on whether participants have ever used a commercially available self-collection kit (eg, Home Access HIV-1 Test System and OraQuick In Home HIV Test) and the type of test kit they have used or their reasons for never using a self-collection kit; *PrEP knowledge, use, and intentions:* questions will be adapted from recent studies of PrEP attitudes among MSM [95-97] to collect data on whether participants have heard about PrEP, are currently using PrEP, their previous use of PrEP, reasons for never using or discontinuing PrEP, access to PrEP, and intentions for future use of PrEP; *bacterial STI testing history:* participants will be asked about whether they have ever been tested for bacterial STIs, the time frame of their most recent tests, the location of their most recent tests, different anatomical sites at which they have been tested, whether they have ever been diagnosed with any STIs in the past, and if so, whether they received treatment or their reasons for never testing [98,99]; *sexual behavior:* data will be collected on relationship status, the number of sex partners with whom participants have had condom-less anal or oral sex in the past 3 months, and whether any of those partners were known to be positive for HIV or other STIs [100,101]; *knowledge of transmission and prevention of HIV and other STIs:* the 27-item STD-KQ will be used to assess participants’ knowledge about different STIs [92]; *perceived risk of contracting HIV and other STIs:* participants will be asked to indicate how concerned they are about contracting HIV and other STIs on a 10-point scale ranging from not concerned at all to very concerned [102]; *experiences with medical care:* the Group-Based Medical Mistrust Scale will be used to assess participants’ previous experiences of racial discrimination and feelings of discomfort and suspicion they might have toward health care personnel and medical treatments [103]; *theoretical willingness and perceived ability to self-collect and return biological specimens:* Likert-item questions will be used to assess participants’ intentions to self-collect and return each of the 5 different types of biological specimens similar to previous studies [81,90], as well as their confidence to complete these activities using simple step-by-step written instructions accompanied by color images; *substance use and psychological distress:* participants will be asked about their alcohol, tobacco, and other drug use in the past 6 months and to self-report depressive symptomology on the revised Center for Epidemiologic Studies Depression Scale [104]. The baseline survey will take approximately 30 min to complete, and participants will receive an incentive of US $40 in the form of an Amazon gift card.

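### Knowledge is measured as a score but compared between groups with chi-square tests, which are valid on a grouped score but inefficient and give no size of difference

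*Protocol article*

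**What the plan says.** The instrument is described under Phase 1 Procedures: "the 27-item STD-KQ will be used to assess participants’ knowledge about different STIs". The Phase 1 Analytic Plan, under Information, then has two consecutive items. The first creates a number for each man: "Scores for the knowledge of transmission and prevention of HIV and other STIs will be formulated for each participant". The second fixes the comparison: "Variations in knowledge levels across categories of selected characteristics will be assessed using chi-square tests for homogeneity".

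The comparison is a listed outcome. Phase 1 Outcomes, Information item 3, begins "Variations in knowledge levels across categories of selected characteristics (eg, age, race and ethnicity, educational level, sexual orientation" and goes on to testing history, relationship status, sexual behaviors, experiences with medical care, substance use and psychological distress.

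The sample is 100 men (Participant Recruitment). By race it is to be "50 black and 50 white including those of Hispanic ethnicity" (Study Overview, Aim 1).

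The only summaries named for numeric variables are "means, medians, and interquartile ranges for continuous variables, and counts and proportions for categorical variables". The sentence assigns these to describing the demographic and behavioral make-up of the sample, not to comparing knowledge between groups.

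**The concern.** A chi-square test for homogeneity compares the distribution of a categorical variable between groups. The plan applies it to a quantity that it has just defined as a numeric score. To run the test, the score has to be put into categories, and differences between men within the same category are then discarded. With three or more categories, the test also ignores their order and spends extra degrees of freedom on patterns other than a shift in knowledge.

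Two things are at stake. The first is sensitivity. The sample is fixed at 100, so the choice of analysis is the main remaining way to gain precision. The second is the output. The article says the results are to serve as formative data for planning programs (Conclusions). A planner would want to know how many points one group scores below another and how uncertain that figure is. A chi-square p-value gives neither.

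**Working it through.** The article states no power, alpha, SD or target difference for this comparison, so there is no figure of its own to reproduce.

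**Inputs from the article.** 27 items; 100 men; the race comparison at 50 v 50, which is the most favorable two-group split.

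**Assumptions, not in the article.** Two-sided alpha 0.05; a roughly normal score with equal SD in the two groups; for the simulation, one point per item (range 0-27), mean 16 and SD 4.5.

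**Step 1: reference difference.** The difference that a comparison of means detects with 80% power at 50 per group is

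d = (1.960 + 0.842) × √(2/50) = 2.802 × 0.2 = 0.56 SD.

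The noncentrality of the comparison of means is 50 × 0.56²/2 = 7.85.

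**Step 2: median split, small-difference limit.** The efficiency relative to comparing means is 2/π = 0.637, a loss of 36%. Under normality the median is the best single cut: cuts at the 40th, 30th and 20th percentiles keep 62%, 58% and 49%.

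**Step 3: median split at d = 0.56.** The proportions above the cut are Φ(0.28) = 0.61 and 0.39. The chi-square noncentrality is 4.87, so the information kept is 4.87/7.85 = 62%. This is close to the limit in Step 2.

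**Step 4: more levels at d = 0.56.** With k equally filled levels, noncentrality = 50 × Σ[(a−m)² + (b−m)²]/m. Here a and b are the two groups' probabilities for a level and m is their mean. Power comes from the noncentral chi-square with k−1 degrees of freedom.

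| Analysis | Noncentrality | Information kept | Power | Men per group for 80% power | Effective sample size kept |
|---|---|---|---|---|---|
| Score compared directly | 7.85 | 100% | 80% | 50 | 100% |
| Median split | 4.87 | 62% | 60% | about 81 | 50/81 = 62% |
| Tertiles | 5.99 | 76% | 58% | about 81 | 50/81 = 62% |
| Quartiles | 6.45 | 82% | 55% | about 85 | 50/85 = 59% |

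Tertiles and quartiles keep more information than a median split, with losses of 24% and 18%. The added degrees of freedom cancel that gain. In effective sample size, the loss runs from 36% (the median-split limit in Step 2) to 41% (quartiles).

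**Step 5: simulation.** This used a rounded 0-27 score, 50 per group and 3,000 runs at d = 0.56. A second simulation used d = 0.57.

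| Test | Power, d = 0.56 | Power, d = 0.57 | Type I error |
|---|---|---|---|
| t-test | 80% | 81% | 4.9% |
| Wilcoxon | 78% | 80% | 4.4% |
| Chi-square, median split | 63% | 65% | 5.4% |
| Chi-square, tertiles | 60% | 61% | 4.8% |

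Formula and simulation agree to within a few points. The last column shows that the grouped chi-square test holds its error rate. Its fault is lost efficiency.

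**The case against.** The strongest reply is that nothing here is wrong in the strict sense. The plan separates the score (item 2) from knowledge levels (item 3), so grouping is evidently intended, and a chi-square test on grouped levels is valid. Cut-points may well be set in the full protocol or analysis plan, which are not shown. The study calls itself exploratory and claims no power. Its aims concern acceptability and feasibility of specimen return, so a less sensitive knowledge comparison threatens neither. All of this stands, and it is why the point is minor. It does not remove the point: the test is stated in the text, and whichever cut a fuller document defines, the efficiency loss remains.

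Several stronger readings are tempting, and the article does not support them.

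- **Raw scores will be cross-tabulated.** With 28 possible scores and two groups there would be 56 cells and an average expected count of 100/56 = 1.8. The article never says this will be done, and its reference to levels points the other way. The 0-27 range is itself an assumed scoring rule.
- **The p-values are invalid.** On the grouped reading, simulated type I error is about 5%.
- **More than a third of the information is lost, whatever the cut.** That figure needs a normal score and a median split. For tertiles and quartiles the information loss is 24% and 18%.
- **The order of levels is always ignored.** A median split has only two levels, so it has no order to ignore.
- **Chi-square is the least sensitive option available.** Only a few tests were compared, under one mean-shift scenario.
- **Missing cut-points are an omission.** A condensed article commonly leaves these to the full plan.

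**Conclusion.** The point holds as one of efficiency and reporting. The plan builds a score and then fixes a test that needs the score to be grouped. At 50 v 50 and a difference of about 0.57 SD, this lowers power from about 80% to about 60-65% for a median split or tertiles. It is equivalent to giving up about 36-41% of the sample. It also leaves the difference in knowledge without an estimate or interval.

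These sizes rest on a roughly normal score, equal SDs, two-sided alpha 0.05, a pure shift between groups and a balanced two-group comparison. The article gives none of these except the 50 v 50 split by race. Characteristics with more than two categories, or with unequal groups, were not computed.

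Severity is minor: a secondary comparison in an exploratory study, with no false-positive problem and no effect on the two aims.

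**What to change.** Change the sentence for Information item 3 in the Phase 1 Analytic Plan. Compare the knowledge score itself across the listed categories, reporting mean differences with 95% confidence intervals from linear regression or ANOVA. Add a Wilcoxon test (two categories) or Kruskal-Wallis test (three or more) as a check that does not rely on normality. If knowledge levels are still wanted for presentation, keep the chi-square test as a supplementary analysis and set the cut-points before the data are seen.

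The outcome as defined, variation across categories of characteristics, stays the same. The cost is one changed sentence, with no new data, no extra participants and no change to the survey.
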